# Effect of a Baduanjin intervention on the risk of falls in the elderly individuals with mild cognitive impairment: a study protocol for a randomized controlled trial

**DOI:** 10.1186/s12906-023-04050-4

**Published:** 2023-07-13

**Keywords:** Baduanjin, Falls, MCI, Randomized controlled trial, RCT protocol

## Abstract

**Background:**

Falls are a global public problem and may be an important cause of death in older adults. However, older adults with mild cognitive impairment(MCI) are more likely to fall and suffer more damage than older adults with normal cognitive function, which shows the importance of preventing falls. More and more evidence shows that Baduanjin can improve the balance function of the elderly and reduce the risk of falls in the elderly with MCI, but the mechanism is still unclear. The main purpose of this study is to verify the intervention effect of Baduanjin training on the risk of falls in elderly people with MCI and to elucidate the underlying mechanism of Baduanjin training in reducing the risk of falls in MCI patients.

**Methods:**

In this prospective study, outcome assessor-blind, three-arm randomized controlled trial, a total of 72 eligible participants will be randomly allocated (1:1:1) into the 12-week Baduanjin exercise intervention (60 min per session, three sessions per week), the 12-week brisk walking group(60 min per session, three sessions per week) or the 12-week health education group. Primary outcome is the Fall-Risk Self-Assessment Questionnaire(FRQ), and secondary outcomes are fall efficacy index, gait assessment, balance function, lower limb muscle strength, cognitive function, activities of daily living(ADL) and MRI scans. In addition to the MRI scans, which will be measured before and after the intervention,other primary and secondary outcomes will be assessed at baseline, 6 weeks, and 12 weeks (at the end of the intervention) and after an additional 12-week follow-up period. The mixed linear model will be conducted to observe the intervention effects.

**Discussion:**

This trial will investigate the effect of Baduanjin exercise on the prevention of falls in elderly individuals with MCI, explore the imaging mechanism of Baduanjin exercise to reduce the risk of falls in elderly individuals with MCI from the perspective of vestibular neural network, and provide strong evidence for Baduanjin exercise to reduce the risk of falls in elderly individuals with MCI, as well as provide new ideas and approaches for the central mechanism of Traditional Chinese Medicine(TRC) rehabilitation methods to intervene in falls in elderly.

**Trial registration:**

Chictr.org.cn, ID: ChiCTR2200057520. Registered on 14 March 2022, https://www.chictr.org.cn/showproj.html?proj=146592.

## Introduction

### Background

According to data from the World Health Organization, falls account for over 38 million disability-adjusted life years lost each year and are the second greatest cause of unintentional injury deaths after traffic accidents [1]. Approximately 15% of people over 65 years old had fallen at least once in the past 12 months [2]. Falls in elderly individuals are a leading cause of death [3] and can result in serious injuries such as fractures, joint dislocations, sprains, strains, and concussions [4]. Older persons who have MCI are at a higher risk of falling [5, 6]. Compared to older people with normal cognitive function, MCI increases the incidence of falls by more than two times [7, 8], and hip fractures after a fall are three times more common [9]. This shows that older people with MCI are at higher risk of falls, are facing a more hazardous situation, and require focused research and attention.

The mechanisms by which falls occur are complex, with the vestibular nerve pathway playing a key role. External receptors transmit signals via the vestibular nerve to the vestibular nucleus and cerebellum in the corresponding brainstem, where they are integrated and processed with other sensory information (e.g. visual information, other proprioceptive information). Multiple neural pathways and central loops transmit information to higher levels of the brain, where it is encoded and processed for decision-making, and ultimately the motor output system sends nerve impulses to control the skeletal muscle system to maintain balance and postural correction [10]. The vestibular circuit is plastic and enhancing sensory input and neuromuscular response activity can improve vestibular function, thereby reducing the risk of falls.

According to a new study published in JAMA, exercise interventions are the most effective way to lower the risk of falls in older persons [11]. A Cochrane systematic review involving 23,407 participants from 108 randomized controlled trials has provided strong evidence that exercise is helpful in reducing falls in community-dwelling older adults [12]. Due to the decline in physical strength and cognitive function in elderly individuals with MCI, it is not suitable to perform high-intensity, complex, or high-agility movements. Baduanjin is an exceptional representative from of traditional Chinese sports therapy, with the characteristics of harmony of body and mind and mutual support of body and spirit. Baduanjin movements are simple and suitable for elderly individuals with MCI to practice, and Baduanjin is practiced by a diverse group of individuals. Studies suggest that Baduanjin can significantly improve memory, executive function, and processing speed in older people [13, 14]; it can also improve balance, leg strength, and mobility and reduce the risk of falls [15–17].However, the mechanism by which Baduanjin reduces the risk of falls in MCI patients remains unclear.

The mechanism by which Baduanjin reduces the risk of falls may be achieved by modulating vestibular nerve pathways. Studies have shown that movement activates areas of the anterior temporal lobe, middle temporal gyrus, superior temporal gyrus, insula, cingulate gyrus, caudate nucleus, and corpus callosum. Exercise training in T2-weighted images modulates functional connectivity in core brain regions of the vestibular neural pathway [18]. In addition, exercise slows neurodegeneration in the cerebellum, activates cortical neural circuits in the cerebellum, and assists the vestibular pathway in the precise localization of movements [19]. Previous studies have suggested that MCI patients have reduced functional connectivity in the right middle temporal gyrus, right parietal limbic angular gyrus, and right anterior cingulate gyrus and gyrus after Baduanjin training. In the brisk walking group, MCI patients had significantly increased functional connectivity in the right inferior parietal limbic angular gyrus and decreased functional connectivity in the right middle temporal gyrus relative to the health education group [20]. Another study showed an increase in gray matter volume in the right hippocampus and an increase in resting-state functional connectivity between the hippocampus and the right angular gyrus in MCI patients after Baduanjin training compared to brisk walking training [21].

Some previous studies have focused on the improvement of cognitive function in elderly people with MCI but not on the brain network mechanisms by which Baduanjin affects falls in elderly people with MCI [20–22]. Moreover, due to the distributed nature of vestibular neural networks, although the existence of pathways had previously been identified in the laboratory, there was no precise definition of their extent and localization, and it was not until 2020 that an accurate imaging map of vestibular neural networks was obtained [23]. Therefore, previous studies only revealed that some brain regions of the vestibular neural network were associated with the cognitive intervention effects of Baduanjin but did not systematically and thoroughly investigate the role of this network as a whole in reducing the risk of falls in senior MCI patients.

We intend to carry out a prospective, randomized controlled trial (RCT) to examine the effects and mechanisms of three months of Baduanjin training on the risk of falls in elderly individuals with MCI. The main goal of this trial is to verify the intervention effect of Baduanjin training on the risk of falls in elderly people with MCI and to explore the mechanism of Baduanjin in reducing the risk of falls in elderly individuals with MCI from the perspective of functional connectivity of the vestibular neural network.

We hypothesize that Baduanjin training could reduce the risk of falls in older adults with MCI compared with brisk walking and no specific exercise intervention. With neuroimaging, we hypothesize that differential functional connection changes will be observed between the Baduanjin training and the brisk walking group and the health education group.

## Methods

### Study design

The design of this study is a three-arm RCT in a 1:1:1 allocation ratio with allocation concealment and assessor blinding. A total of 72 eligible participants will be randomly assigned to the 12-week Baduanjin exercise intervention (60 min per session, three sessions per week), the 12-week brisk walking group(60 min per session, three sessions per week) or the 12-week health education group. In addition to the MRI scans, which will be measured before and after the intervention,other primary and secondary outcomes will be assessed at baseline, 6 weeks, and 12 weeks (at the end of the intervention) and after an additional 12-week follow-up period. The study procedure and outcome assessment schedule for this trial are presented in Figs. 1 and 2.

**Fig. 1 Fig1:**
[figure not shown]
Flow chart of the trial

**Fig. 2 Fig2:**
[figure not shown]
Schedule of enrolment, assessments, and interventions

### Study population

The study population is a community of older adults with MCI. The diagnostic, inclusion, and exclusion criteria for the study sample are as follows.

### Diagnostic criteria

The criteria for MCI are as follows [24]: (1) cognitive impairment confirmed by a patient or insider, or by an experienced clinician; (2) impairment in one or more cognitive domains (memory, language, visuospatial, or executive function); (3) normal activities of daily living; and (4) no dementia.

#### Inclusion criteria

The eligible participants must meet the following criteria for inclusion: (1) diagnosed with MCI; (2) aged 60 years or older; (3)Montreal Cognitive Assessment (MoCA) score of<26points (if the years of education are ≤ 12 years, add 1 point to the score); (4)had no regular physical exercise for at least half a year (regular exercise means exercise with a frequency of at least three times a week and at least 20 min per session);(5)no contraindications to MRI scans; and (6) provided informed consent.

### Exclusion criteria

The exclusion criteria are as follows: (1) patients with hypertension with uncontrolled blood pressure (systolic blood pressure greater than 160 mm Hg or diastolic blood pressure greater than 100 mm Hg); (2) history of alcohol or drug abuse; (3) depression-induced cognitive impairment, Beck Depression Scale > 4 points; (4)cognitive impairment due to other causes such as poisoning or drugs;

(5)history of mental illness (including personality disorder, schizophrenia, etc.), severe aphasia or audio-visual disorders, severe organ failure, history of coronary artery disease, musculoskeletal disorders, or other exercise contraindications; and (6) participation in another clinical study.

### Withdrawal criteria and management

Participants will be allowed or required to withdraw from the study based on the following criteria: (1) major violations of the study protocol; (2) suffering from a serious disease, preventing the continuation of the trial; (3) sufferiing from serious adverse events related to the research during the study period; and (4) voluntary request to be withdrawn from the trial.

#### Recruitment

Participants will be recruited from Dalang Community Center and Xingdong Community Center in Shenzhen city through a combination of online and offline efforts, including internect recruitment, posting posters, sending leaflets, and setting-up onsite recruitment stations. Potentially eligible individuals will first complete a screening by community doctors in the Community Health Service Center to determine their eligibility according to the inclusion and exclusion criteria. The eligible individuals who are interested in participating in the study will have an informed discussion with trained research assistants. The research assistants will obtain written informed consent from individuals willing to participate in the study before starting the baseline assessment [25].

#### Randomization, allocation concealment, and blinding

After the baseline assessment, the eligible participants will be randomly assigned to the Baduanjin group, the brisk walking group, or the health education group. The simple random allocation sequence will be generated using the PLAN procedure of the statistical software SAS V.9.0 and will be managed by an independent research assistant who is not involved in the recruitment, evaluation, and intervention of the participants. The eligible participants will be informed of their allocation result by the independent research assistant via telephone [26]. We cannot blind participants, exercise coaches, or intervention supervisors to the assigned treatment, but outcome evaluators and data statisticians will be blinded to group allocation.

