### Intervention

#### Baduanjin group

Based on the health education group, participants in the Baduanjin group will receive 12 weeks of Baduanjin exercise training with a frequency of 3 days a week and 60 min a day [27, 28]. Baduanjin exercise training will be assigned at two community centres (Dalang Community Centre and Xingdong Community Centre in Shenzhen city) with 30–40 individuals per centre. Two professional coaches who have taught Baduanjin for at least 5 years will be hired to guide the training of the trainees. The training scheme of the Baduanjin exercise is planned as previously described in detail and consists of 10 postures [25] (including the preparation and ending postures).

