### Sample size

The results of a previous systematic review showed that the standardized mean difference of the fall risk of the elderly with Baduanjin exercise intervention was − 0.59 [-0.83, -0.35] [36], which was used as a reference to calculate the sample size of the effect size of this study. The significance level will be set at α = 0.05, and the power will be 0.80. Using Gpower 3.9 software, we calculated that a sample size of at least 20 patients per group is needed, and considering a 20% drop-out rate, which means 24 patients per group, the total sample size required for this study is 72 cases.

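### A simple random sequence for 72 people at two centres secures neither the planned 24 per arm nor balance of the arms by centre

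*Protocol article*

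**What the plan says.** - **Allocation method** (Randomization, allocation concealment, and blinding): "The simple random allocation sequence will be generated using the PLAN procedure" of SAS. An independent research assistant holds the list and tells participants their group by telephone. No blocking, stratification or fixed totals are mentioned.
- **Ratio** (Study design): a "three-arm RCT in a 1:1:1 allocation ratio with allocation concealment and assessor blinding".
- **Arm size** (Sample size): "we calculated that a sample size of at least 20 patients per group is needed", then "considering a 20% drop-out rate, which means 24 patients per group", and "the total sample size required for this study is 72 cases".
- **Centres** (Recruitment): participants come from two community centres in one city.
- **Delivery** (Baduanjin group): "Baduanjin exercise training will be assigned at two community centres", with 30 to 40 people at each. Two coaches are hired for the Baduanjin classes. Walkers are instructed beforehand and then train at home (Brisk walking group).
- **Model** (Statistical analysis): the mixed model for the primary outcome lists group, time, sex, age and education, plus an open category of further confounders. Centre is not named.

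**The concern.** In the usual sense of the term, a simple random sequence gives each person an independent one-in-three chance of each arm. The 1:1:1 ratio then holds only on average, and nothing ties the arms to the 24 on which the drop-out allowance is built. Nor does anything tie the mix of arms within a centre to the mix in the other, although recruitment and the Baduanjin classes are organised by centre. In a trial of 72, a lopsided draw is not a remote possibility. It can use up the drop-out margin of one arm on the day of randomisation, or leave two arms with clearly different centre composition.

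A separate inconsistency sits in the same part of the plan. A class size of 30 to 40 at each of two centres means 60 to 80 people in Baduanjin training, against a Baduanjin arm of 24.

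**Working it through.** **Inputs.** Total 72, three arms, 1:1:1; minimum 20 per arm; 24 per arm planned; two centres; standardised mean difference (SMD) 0.59; two-sided alpha 0.05 (Sample size, Statistical analysis, Recruitment). The split between centres is not given; 36 each is assumed.

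**The plan's own figures.** 20 × 1.2 = 24 and 3 × 24 = 72 reproduce. Dividing by the retained fraction would give 20 / 0.8 = 25 per arm. The 20 itself does not follow from an SMD of 0.59 at two-sided alpha 0.05 and 80% power, which needs 47 per group by the two-sample t test. That is a separate and larger matter; here 20 serves only as the plan's own threshold.

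**Arm sizes if the sequence is unrestricted.** The counts (a, b, c) follow a multinomial distribution:

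P(a, b, c) = 72! / (a! b! c!) × (1/3)^72

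Each arm has mean 72/3 = 24 and SD √(72 × 1/3 × 2/3) = √16 = 4.0. Summing over all outcomes:

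| Event | Probability |
|---|---|
| Exactly 24/24/24 | 1.1% |
| Smallest arm below 20 | 38.1% |
| Smallest arm at or below 20 | 54.9% |
| One pre-named arm at or below 20 | 19.2% |

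The expected smallest arm is 19.9 and the expected largest 28.2. An arm that starts at 20 and loses 20% ends at 20 × 0.8 = 16; an arm of 24 ends at 24 × 0.8 = 19.2.

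**Arm sizes if totals were fixed.** A random permutation of 72 slots with 24 per arm, which the PLAN procedure can also produce, gives 24/24/24 every time. None of the probabilities above then applies.

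**Centre balance, 36 per centre assumed.** For each arm take the share of its members who come from the first centre, and compare the largest share with the smallest.

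- Unrestricted: two independent multinomials of 36. The gap is 20 points or more in about 37% of sequences. For one given pair of arms it is 18%.
- Totals fixed at 24, no stratification: multivariate hypergeometric. The gap is 20 points or more in about 42% of sequences. Shares move in steps of 1/24, so the threshold is met at 5 people (5/24 = 20.8 points).

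**Cost in power.** Pairwise two-sided t test at SMD 0.59: 51.6% with 24 v 24, and 50.7% averaged over unrestricted sequences. The difference is 0.9 points.

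**Possible shift from centre imbalance.** The documents give no centre effect. Assuming 0.1 to 0.5 SD, a 20-point imbalance moves an unadjusted contrast by 0.20 × 0.1 = 0.02 SD to 0.20 × 0.5 = 0.10 SD.

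**Effect of the fix.** With blocks no larger than 6 within each centre, an unfinished block of r people leaves an arm short of its expected r/3 by at most 4/3 (at r = 4, with none in that arm). Over two centres the shortfall is at most 8/3, so had all 72 been allocated this way every arm would have at least 24 − 2.67 = 21.3, that is 22. The probability of an arm at or below 20 falls from 54.9% to 0.

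**The case against.** The best case for the plan has several parts.

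- **The word may be loose.** *Simple* need not mean unrestricted. The article also says 1:1:1 and 24 per group, and the named procedure can fix totals. This stands: the arm-size probabilities are conditional on one reading. It does not rescue centre balance, which fixed totals leave open.
- **Exactly 24 is not required.** The plan asks for at least 20, so the 1.1% describes the method and is not a failure rate. A reader might infer from the 55% that an arm is more likely than not to miss the minimum. It is not: an arm of 20 meets that minimum, and the chance of falling below it is 38%.
- **The power cost is trivial.** This stands. The low power comes from the sample size calculation, not from uneven arms.
- **The comparison is not biased.** A reader might infer bias from chance imbalance. Simple randomisation is valid and unbiased in expectation; the imbalance belongs to the particular sequence drawn.
- **Coach is not a chance confounder.** Class coaching is part of the Baduanjin arm by design, and the article does not say that each centre has its own coach. Stratifying by centre would not separate coach from arm.
- **Centre may matter little, or already be covered.** Both centres are in one city, staff of one hospital assess outcomes, and the open category of confounders does not exclude centre. That limits the weight of the point. Still, an unnamed covariate fixes nothing in advance.
- **The class-size sentence has nothing to do with randomisation.** True, but the conflict with 24 is real. About 36 per centre (72/2) would fit total enrolment; the article does not say that this was meant.

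**Conclusion.** The point holds as a modest design weakness that is cheap to improve. As worded, the method does not secure the arm sizes on which the sample size rests, and under neither reading does it secure centre balance. If unrestricted, the chance that some arm starts below 20 is 38%. If totals were fixed at 24, that risk is nil and the description needs correcting. The centre gap of 20 points or more, in about 37% or 42% of sequences, rests on the assumed 36 per centre and on taking the widest gap among three arms. Whether such a gap matters depends on a centre effect that the documents do not report. The documents do not support a claim of an invalid trial, a biased estimate or a material loss of power.

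**What to change.** 1. State whether the arm totals were fixed, and replace *simple* if they were.
2. For allocations not yet made, use permuted blocks of randomly varying size (for example 3 and 6), stratified by the two centres. The same independent assistant generates and holds the list and keeps the telephone notification.
3. Name centre as a fixed factor in the primary mixed model, for all participants.
4. Reconcile the 30 to 40 people per centre under Baduanjin group with the 24-person arm under Sample size.

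**Cost.** A new list from the same software, one model term and two text corrections. Allocation becomes slightly predictable at block ends, more so with blocks of 3 and unblinded participants and coaches; varying, undisclosed block sizes and central telephone notification limit this. The article gives the implementation period as March 2022 to March 2024 and appeared in July 2023, so few allocations may remain. Those already made cannot be repaired, and the floor of 22 per arm is not guaranteed after a switch partway through. For people already allocated, only the centre term helps.

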### Intervention

#### Baduanjin group

Based on the health education group, participants in the Baduanjin group will receive 12 weeks of Baduanjin exercise training with a frequency of 3 days a week and 60 min a day [27, 28]. Baduanjin exercise training will be assigned at two community centres (Dalang Community Centre and Xingdong Community Centre in Shenzhen city) with 30–40 individuals per centre. Two professional coaches who have taught Baduanjin for at least 5 years will be hired to guide the training of the trainees. The training scheme of the Baduanjin exercise is planned as previously described in detail and consists of 10 postures [25] (including the preparation and ending postures).

